## Abstract

**Background:**

Extracorporeal blood purification with CytoSorb has been increasingly used as an adjunctive therapy in several hyperinflammatory critical care conditions, as well as to remove elevated levels of myoglobin or bilirubin in patients with rhabdomyolysis or liver failure. Despite the increasing worldwide use of hemoadsorption, data from large international multicenter studies are still lacking.

**Objective:**

The COSMOS (CytoSorb Treatment Of Critically Ill Patients) registry is a company-sponsored registry by CytoSorbents Corporation and CytoSorbents Medical Inc. and will provide a data repository and reporting infrastructure for the surveillance of CytoSorb use in real-world critical care settings in an unselected, critically ill patient population. The gathered data will serve as a comprehensive resource to assess the effects of such therapy on patients’ management.

**Methods:**

The international COSMOS registry is collecting prospective data for patients treated with CytoSorb during routine care in various critical care indications, based on the decision of the treating physicians. Data are collected at baseline, during CytoSorb therapy, 24 hours thereafter, at discharge from the intensive care unit and the hospital, and on day 90. Key outcomes assessed include change in inflammatory biomarkers, vasopressor requirements, fluid balance, organ function and organ support, length of intensive care unit and hospital stay, occurrence of adverse events, and mortality.

**Results:**

The COSMOS registry started with the inclusion of the first patient on July 15, 2022, and is now actively enrolling in 4 countries (Germany, Spain, Portugal, and Italy), with plans to expand to other countries outside of Europe. An initial readout is planned for presentation at an international Critical Care conference in 2024.

**Conclusions:**

The COSMOS registry is intended to provide comprehensive real-world data on patient outcomes with CytoSorb in various critical care indications, thereby contributing to optimization of patient selection, timing of initiation, and dosing of hemoadsorption treatment.

**Trial Registration:**

ClinicalTrials.gov NCT05146336; https://clinicaltrials.gov/study/NCT05146336

**International Registered Report Identifier (IRRID):**

DERR1-10.2196/55880

## Introduction

### Background and Rationale

Prolonged and excessive inflammation, characterized by the persistent release of several mediators into the blood stream in response to different stimuli, is believed to contribute to multiple organ failure, leading to a high risk of mortality [1,2]. Blood purification has been increasingly used for treating critically ill patients with excessive inflammation and can be considered as an umbrella for different procedures, subdivided into hemofiltration, hemoadsorption, and plasma-processing techniques, including plasmapheresis and plasma exchange [3-5].

The concept of hemoadsorption refers to the adhesion of circulating molecules such as cytokines to the surface of the respective sorbent material. Different hypotheses have been developed to explain possible beneficial effects of removing such mediators from the bloodstream, including lowering pro- and anti-inflammatory mediators below a threshold to limit organ damage [6] and restoration of a cytokine gradient between tissue- and blood-promoting leukocyte chemotaxis [7]. This pathophysiological rationale and the growing number of clinical studies have led to the hypothesis that reducing inflammatory mediators within the systemic circulation could restore immune homeostasis and positively affect patient outcomes. Currently, there are several extracorporeal technologies available that offer potential benefits in blood purification for managing life-threatening conditions. These include CytoSorb (CytoSorbents), oXiris (including the AN69-ST; Baxter), Jafron HA-series (including HA-230, HA-280, HA-330, HA-330-II, and HA-380; Jafron), Seraph 100 Microbind Affinity Blood Filter (Seraph100; ExThera Medical), and Polymyxin B hemoperfusion (PMX-HP; Toraymyxin, Toray Medical Co., Ltd.). These devices vary in their specific modes of action and target substances for removal, approved indications, and documented clinical experiences, including any potential impact on drug removal [8-10].

The CytoSorb device is a Conformité Européenne labeled whole blood hemoadsorption device. The device was registered in 2011, and the number of patients treated with CytoSorb has continued to grow.

A recent randomized controlled trial (RCT) in healthy volunteers provided definitive mechanistic evidence of CytoSorb’s ability to decrease systemic cytokine levels after intravenous administration of endotoxin in an established sepsis model [11]. These findings support the approved indications of CytoSorb therapy for the treatment of a variety of clinical conditions in which excessively high plasma levels of inflammatory mediators occur, such as septic or vasoplegic shock, acute respiratory distress syndrome (ARDS), and critical illness requiring extracorporeal membrane oxygenation (ECMO) therapy. Additional application fields for CytoSorb include use of the device for removal of elevated levels of bilirubin and myoglobin in patients with life-threatening conditions, such as liver failure [12] or rhabdomyolysis [13], as well as the intraoperative removal of ticagrelor and rivaroxaban during cardiothoracic operations with cardiopulmonary bypass [14].

Despite the increasing worldwide use of blood purification therapies, large international, multicenter studies and robust evidence of clinical outcome improvement are still lacking [15,16]. Consequently, questions about the appropriate application modalities, especially regarding timing and dose, remain unanswered. Also, some conflicting data showing neutral or even negative outcomes have been published, underlining the need for further conclusive evidence generation [17-19]. A recent systematic review showed no mortality benefit of the therapy in a very heterogenic patient group and underlined the need to systematically identify patients likely to respond to the therapy with clinical benefits in a reproducible manner [16].

The hemoadsorption device can be easily integrated into concomitant continuous renal replacement therapy or into a dedicated hemoperfusion circuit (Figure 1), as well as into a bypass within the ECMO circuit or a cardiopulmonary bypass circuit.

**Figure 1 figure1:**
[figure not shown]
Setup integration of CytoSorb into different platforms: (A) hemoperfusion; (B) continuous renal replacement therapy (CRRT) predialyzer; (C) CRRT postdialyzer; and (D) extracorporeal membrane oxygenation with bypass.

### Objectives of the COSMOS Registry

The aim of the COSMOS (CytoSorb Treatment Of Critically Ill Patients) registry is to capture real-world clinical use patterns and clinical outcomes associated with the utilization of the CytoSorb device and to help further refine best practices for the therapy. There is a well-known heterogeneity of treatment effects in critically ill patients [20], which is why collecting registry data is a valuable tool, making it easier to identify those patients who would potentially benefit most from the therapy. Also, treatments of critically ill children are included as a predefined subcohort, allowing the collection of multicenter data, thereby expanding the available evidence derived from single-center reports on limited patient numbers. Additionally, the registry will also serve as a crucial part of the postmarket clinical follow-up measures as required by Medical Device Regulation [21].

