## Methods

### Study Setting

The COSMOS registry is an ongoing, observational, prospective, and international data collection platform for patients receiving CytoSorb devices during routine clinical care. Site selection was performed according to experience with the hemoadsorption therapy (total number of treatments per year), usual indications for use, estimated patient number contributions, experience in study conduct and electronic data collection, as well as personnel capacity and overall interest in participation based on a dedicated site qualification questionnaire. The treatment strategy and patient’s management are determined by the physician and not by the registry protocol. For all site personnel, including the principal investigator, subinvestigators, and clinical research coordinators, training on the latest hemoadsorption therapy recommendations is provided to ensure that the users are aware of the current understanding of best practice with CytoSorb and consider these aspects in their decision-making on therapy management [22,23]. Additionally, each investigator is encouraged to review the most recent CytoSorb instructions for use to assess contraindications, warnings, and precautions for treating potential patients. In order to best represent real-world practice and to avoid selection bias, sites are asked to include consecutive patients receiving the CytoSorb device. All clinical data from critically ill patients treated with the device after the date of approval of the institutional review board (IRB) or independent ethics committee (IEC) are considered “prospective data.”

The registry collects patient-level data with the use of the CytoSorb device in the following different clinical indications (Table 1).

The study may be discontinued at the discretion of the investigator (or designee) or sponsor if any of the criteria mentioned in Textbox 1 are met.

**Table 1 table1:** Different indications for CytoSorb included in the COSMOS (CytoSorb Treatment Of Critically Ill Patients) registry.

Category	Clinical indication
Hyperinflammation	Septic shock Hemophagocytic lymphohistiocytosis CRS^a^ Chimeric antigen receptor therapy CRS
Cardio and pulmonary	Cardiogenic shock Acute respiratory distress syndrome Lung failure with venovenous extracorporeal membrane oxygenation and cardiac failure with extracorporeal life support system
Liver and kidney	Acute liver failure or acute-on-chronic liver failure Rhabdomyolysis

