### Eligibility Criteria

The registry population will be comprised of critically ill patients, including children who undergo treatment with the CytoSorb device as part of their routine clinical care. To best represent real-world practice and avoid selection bias, participating sites will ideally include all patients receiving the CytoSorb device consecutively, without preselection (Textbox 2).

Inclusion and exclusion criteria.

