### Analysis and Statistical Methods

Descriptive statistics and patient data listings will be used to summarize the data. Continuous variables will be summarized by nonmissing values (n), mean and SD (in case of normal distribution), median, 25th and 75th percentiles (in case of nonnormal distribution), and minimum and maximum. Categorical variables will be summarized by frequencies and percentages. Stratification of descriptive categories within treatment groups may occur if such elaborations are thought to be useful. Inferential statistical tests may be used, as appropriate, with an α critical value of .05 to indicate statistical significance. Inferential statistical tests will be 2-sided, unless specified otherwise. Also, 95% CIs may be used to compare event rates to a historical and clinically meaningful standard or to investigate the course of biomarkers (or certain laboratory values) after CytoSorb therapy. Multivariate analysis may be used to determine independent predictors of study outcomes. Missing data is unavoidable for critically ill patients treated in the intensive care unit (ICU). The principle of analyses is to only include the nonmissing observations. For inflammatory biomarkers or laboratory values that are highly associated with the use of hemoadsorption devices, sensitivity analyses will be performed by applying a multiple imputation method under the missing-at-random assumption.

Unless specified otherwise, minimum and maximum will be displayed to the same level of precision as the observed value. Mean and median will be displayed to 1 level of precision greater than the observed value. The SD and SE will be displayed to 2 levels of precision greater than the observed value. All *P* values will be rounded to and displayed as 3 decimals. If a *P* value less than .001 occurs, it will be shown in tables as <.001.

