## Discussion

### Overview

The previous CytoSorb international registry collected patient data from May 2015 to December 2020 and was independently led as an investigator-initiated project by the Centre for Clinical Studies at the Jena University Hospital, Germany [24]. At its closure, 46 sites had included a total of 1434 patients showing improvements in cardiovascular and pulmonary Sequential Organ Failure Assessment scores and a reduction in procalcitonin, C-reactive protein, and interleukin-6 levels [24]. However, several important parameters were not captured, for example, lactate and hemodynamic data, due to a lack of knowledge of hemoadsorption treatment characteristics at the time of conceptualization of the project. Also, the definition of sepsis and septic shock changed in 2016 [25]. Furthermore, other indications for blood purification, including bilirubin and myoglobin removal, were not yet covered at the time by the Conformité Européenne label and were therefore not considered in the initial design of the Jena registry.

Existing literature in the field of CytoSorb treatment mainly consists of smaller studies, case series, and case reports [16], including studies that showed neutral or negative results [17-19]. In the following paragraphs, we summarize the current understanding of the pathophysiology and rationale behind the most common use of CytoSorb in critically ill patients. Of note, so far, evidence is still scarce with a lack of larger RCTs in the field. In general, pooled analysis of such heterogenous patient groups is difficult, especially given the methodological limitations of these studies [26].

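### A registry of treated patients only cannot show who benefits most from CytoSorb, and the objectives should be limited to description, association and prognosis

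*Protocol article*

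**What the plan says.** The eligibility criteria require use of the device and consent, and "participating sites will ideally include all patients receiving the CytoSorb device consecutively, without preselection". Under Study Setting, treatment strategy and patient "management are determined by the physician and not by the registry protocol". The article describes no untreated or concurrent group.

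The aims are worded at several strengths:

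- Objectives of the COSMOS Registry states an associational aim, "clinical outcomes associated with the utilization of the CytoSorb device". It then cites heterogeneity of treatment effects as the reason registry data are valuable, "making it easier to identify those patients who would potentially benefit most from the therapy".
- The Abstract's Objective calls the data a "comprehensive resource to assess the effects of such therapy on" the management of patients.
- The Abstract's Conclusions expect the registry to help improve patient selection as well as timing and dosing.

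Analysis and Statistical Methods is mainly descriptive. It adds three optional inferential tools: multivariate models for predictors of outcome, confidence intervals for the course of biomarkers after therapy, and a benchmark comparison in which "95% CIs may be used to compare event rates to a historical and clinically meaningful standard". The standard is not named, and adjustment is neither stated nor excluded.

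Strengths and Limitations says in general terms that real-world evidence has limits. The final Conclusions leave specific hypotheses to possible future randomised trials embedded in the registry.

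**The concern.** Benefit is the difference between a patient's outcome with the device and the outcome without it. The registry observes only the first. A model fitted to treated patients shows who does well or badly after treatment. It cannot separate good prognosis from good response. An aim that appeals to heterogeneous treatment effects therefore asks for something the design does not supply.

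The optional tools do not close this gap. A comparison with a historical rate mixes any device effect with differences in indication, severity, age, period and care. A before-after course has no untreated course beside it. If such results are read against the stated objectives, a low-risk subgroup could be taken for a responding one, or a favourable case mix for a device effect. Readouts are at least annual and enrolment is under way, so the wording matters now.

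**Working it through.** **The plan's own figure.** The Results section gives no sample size calculation, only a projection: 300 per year × 10 years = 3000, which reproduces. Actual enrolment was 199 patients from July 15, 2022 to August 1, 2024, or 2.05 years. That is 199 / 2.05 ≈ 97 per year, about 970 in ten years. The checks below use n = 199 (current), 1000 (about ten years at the present pace) and 3000 (the projection).

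The article gives no mortality rates, case-mix distribution or biomarker correlations. All such values below are assumptions.

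**Check 1: can treated-only data show who benefits?** Take two strata with treated mortality of 30% and 60%. The odds ratio between them is (0.60/0.40) / (0.30/0.70) = 3.5. Now vary the untreated mortality, which the registry never sees:

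- untreated 30% and 60%: absolute benefit 0 and 0 points
- untreated 30% and 75%: absolute benefit 0 and 15 points
- untreated 45% and 60%: absolute benefit 15 and 0 points

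The registry data and the odds ratio of 3.5 are the same in all three. The stratum that benefits differs, and no model fitted to the treated patients alone can recover it.

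**Check 2: the historical comparison under zero device effect.** Let the standard be p0 and the registry's expected rate be p = p0 + d, where d comes from case mix alone. With SE = √(p(1−p)/n) and z = |d|/SE, the chance that a two-sided 95% CI excludes p0 is Φ(z − 1.96) + Φ(−z − 1.96).

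Worked case: p0 = 0.40, d = −0.05, n = 199. SE = √(0.35 × 0.65/199) = 0.0338 and z = 1.48, so the probability is 0.315.

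For p0 of 0.40 to 0.50:

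| Case-mix shift | n = 199 | n = 1000 | n = 3000 |
|---|---|---|---|
| none | 5% | 5% | 5% |
| −3 points | 14% | 48-50% | 91-93% |
| −5 points | 29-32% | 89-91% | ~100% |
| −10 points | 82-87% | ~100% | ~100% |
| +5 points | 29% | 89% | ~100% |

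The error can run in either direction, and a larger registry makes it more certain. A shift of 5 points is not extreme: if an eighth of patients came from an indication with 20% mortality instead of one with 60% (assumed), the pooled rate would move by 0.125 × 40 = 5 points. Table 1 of the article lists about 15 indications, and children are included.

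**Check 3: the before-after course under zero device effect.** Standardise the marker and let ρ be its correlation with the later value. If treatment starts when the marker exceeds c, the expected fall is (1 − ρ) × E[X | X > c]. This mean is 0.798 for c = 0 and 1.525 for c = 1.

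- ρ = 0.5: fall of 0.40 SD (c = 0) or 0.76 SD (c = 1)
- ρ = 0.7: fall of 0.24 or 0.46 SD
- ρ = 0.9: fall of 0.08 or 0.15 SD

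At n = 199 the 95% CI for the mean change excludes zero in all six cases. The article states no biomarker threshold for starting treatment, so c is an assumption too.

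**The case against.** The strongest reply is that this is a mainly descriptive registry whose aim sentence is already associational. The sentence on benefit is hedged, the Abstract's Objective refers to effects on patient management and not to efficacy in general, and specific hypotheses are left to embedded trials. Use patterns, safety surveillance and post-market follow-up need no untreated arm. All of that stands. It lowers the weight of the point but does not remove it: the benefit sentence rests explicitly on heterogeneity of treatment effects, the Abstract's Conclusions extend it to patient selection, and the limitations section never says that the comparator is missing. An objective that the design cannot meet is not a detail for an analysis plan.

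Several stronger readings are tempting and are not supported:

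- *That an unadjusted, pooled comparison is planned.* The text only permits the comparison, does not say that it is pooled, allows stratification and is silent on adjustment. Severity and comorbidity scores are collected, and an unseen analysis plan may specify their use.
- *That regression to the mean biases the historical comparison.* It belongs to the before-after courses. Case mix is the main threat to the benchmark.
- *That the authors concede pooling in COSMOS is unsound.* The remark that "pooled analysis of such heterogenous patient groups is difficult" is about the existing literature.
- *That changing case mix would show up as an apparent effect between annual readouts.* Moving 10% of enrolment from 60% to 20% mortality (assumed) shifts the rate by 4 points. At 300 patients per year and 40% mortality (assumed), the half-width for a difference between two annual cohorts is 1.96 × √(2 × 0.24/300) = 7.8 points, so the shift lies well inside sampling error.

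**Conclusion.** The concern holds in a limited form. The registry by itself cannot identify a treatment effect or which patients benefit most, and three statements of aim go beyond that limit: the benefit sentence in the Objectives, the patient-selection claim in the Abstract's Conclusions and, more loosely, the Abstract's Objective. This rests on the design alone and needs no numerical assumption.

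The benchmark comparison is a conditional risk. If it is used without case-mix standardisation, with assumed historical mortality of 40-50%, no device effect and a 5-point case-mix difference, false exclusion of the standard occurs about 30% of the time at 199 patients and about 90% at 1000. For before-after courses, falls of 0.08 to 0.76 SD can arise from regression to the mean alone under the assumed thresholds and correlations. The article does not commit to reading either result as a device effect. The point is that nothing in it prevents that reading and the stated objectives invite it.

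**What to change.** 1. Limit the wording in the Abstract's Objective, the Abstract's Conclusions and the Objectives section to use patterns, outcomes, associations and prognostic factors in treated patients. State in Strengths and Limitations that there is no comparator. Leave benefit and effect modification to the embedded randomised trials that the article already foresees.
2. If a historical standard is used, compare only within indication and separately for adults and children. Fix the benchmark before the readout, standardise for case mix on variables already collected (age, APACHE II or PIM-3, SOFA or PELOD-2), and include the benchmark's own uncertainty in the interval.
3. Report before-after courses as description, not as device effect.

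The cost is mostly wording, since the baseline scores are already in the dataset. The downside is weaker claims, no pooled benchmark and a little more analysis work.

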## Methods

### Study Setting

The COSMOS registry is an ongoing, observational, prospective, and international data collection platform for patients receiving CytoSorb devices during routine clinical care. Site selection was performed according to experience with the hemoadsorption therapy (total number of treatments per year), usual indications for use, estimated patient number contributions, experience in study conduct and electronic data collection, as well as personnel capacity and overall interest in participation based on a dedicated site qualification questionnaire. The treatment strategy and patient’s management are determined by the physician and not by the registry protocol. For all site personnel, including the principal investigator, subinvestigators, and clinical research coordinators, training on the latest hemoadsorption therapy recommendations is provided to ensure that the users are aware of the current understanding of best practice with CytoSorb and consider these aspects in their decision-making on therapy management [22,23]. Additionally, each investigator is encouraged to review the most recent CytoSorb instructions for use to assess contraindications, warnings, and precautions for treating potential patients. In order to best represent real-world practice and to avoid selection bias, sites are asked to include consecutive patients receiving the CytoSorb device. All clinical data from critically ill patients treated with the device after the date of approval of the institutional review board (IRB) or independent ethics committee (IEC) are considered “prospective data.”

The registry collects patient-level data with the use of the CytoSorb device in the following different clinical indications (Table 1).

The study may be discontinued at the discretion of the investigator (or designee) or sponsor if any of the criteria mentioned in Textbox 1 are met.

**Table 1 table1:** Different indications for CytoSorb included in the COSMOS (CytoSorb Treatment Of Critically Ill Patients) registry.

Category	Clinical indication
Hyperinflammation	Septic shock Hemophagocytic lymphohistiocytosis CRS^a^ Chimeric antigen receptor therapy CRS
Cardio and pulmonary	Cardiogenic shock Acute respiratory distress syndrome Lung failure with venovenous extracorporeal membrane oxygenation and cardiac failure with extracorporeal life support system
Liver and kidney	Acute liver failure or acute-on-chronic liver failure Rhabdomyolysis
Infectious disease	COVID-19 Influenza Dengue
Others	Postoperative vasoplegic shock Burns Pancreatitis Overdose drug removal

^a^CRS: cytokine release syndrome.

Study discontinuation criteria.Medical or ethical concernsSafety issues pertaining to adverse device events (ADEs) or serious adverse events (SADEs) unknown to dateChanges in accepted clinical practice making the continuation of a registry unwiseDifficulties in patient recruitmentSponsor’s decision

